### Secondary endpoint

#### *Overall Survival*

Overall survival is defined as the length of time from randomization to death from any cause.

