## **Dose escalation with SIB to intraprostatic/lymphatic GTV in high risk prostate cancer**

### ***Method***

#### **Study design**

The present study will be performed as a single institute prospective consecutive phase II clinical trial with matched historical controls of dose escalation to intra prostatic tumor and, if eligible, to radiological lymph node metastasis in the pelvis.

Patients are recruited consecutively during their consultation at Cancer Centre, Umeå University Hospital, after given both oral and written patient information and due time for consideration.

All patients included in the present study will receive external radiotherapy (RT) of 2,2 Gy to 77 Gy to the prostate in 35 fractions and pelvic nodal radiotherapy of 1,6 Gy to 56 Gy in 35 fractions. A simultaneous integrated boost (SIB) of 84 Gy in 35 fractions (fractional dose 2,4 Gy) will in addition be delivered to macroscopic tumor in the prostate. In case of radiological suspected metastasis in one or more of the pelvic lymphatic nodes according to PET/CT-scan an additional SIB of 70 Gy in 35 fractions (fractional dose 2 Gy) will be delivered to PET-positive nodules.

At baseline QoL questionnaire and baseline symptoms will be collected after given informed consent. Renewed QoL and symptom scoring will be collected at end of treatment and during follow up. A historical control group of 100 consecutive patients receiving external radiotherapy to prostate/pelvic lymph nodes without dose escalation to the intra prostatic macroscopic tumor will be used to compare PFS, OS, LC and QoL. Matching criteria is T-stadium, pre-treatment PSA and GS.

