### **Inclusion:**

- Histologically confirmed high risk prostate cancer with a risk of lymphatic spread >15% according to the MSKCC nomogram (1), previously untreated  
<http://nomograms.mskcc.org/Prostate/PreTreatment.aspx>
- Written informed consent
- > 18 years
- Fiducial gold markers implanted in the prostate (min 3)

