## Endpoints

### Primary endpoint

#### *Progression Free Survival*

Progression free survival is defined as the length of time from inclusion to the first documentation of one of the following:

**PSA progression** defined according to American Society for Therapeutic Radiology and Oncology (ASTRO) Phoenix definition: nadir PSA + 2 ng/mL (on three consecutive measurements with at least one month between each)

or

**Death** due to any cause

or

**Radiological disease progression**, locally or as metastatic disease.

Due to potential “PSA bounce” during the first 24 months after treatment, a PSA rise >2 ng/mL may not be deemed as progression by the treating physician until after the clinical window of a bounce is excluded. The date for progression will then be corrected.

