## **Withdrawal from treatment**

The patient can at any time withdraw from treatment. The date and reason for withdrawal should be reported in the CRF. If a patient is lost to follow up the date and reason for this should be reported in the CRF. Loss of follow-up does not mean that the patient leaves the study. All patients that are randomised should be followed until the end points have been reached - irrespective of further treatment regimes and in accordance with the intention of treatment strategy.

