## **Statistical methods**

Prospective phase II clinical trial with matched historical controls.

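### Overall survival is timed from a randomization the design does not contain, PFS from an inclusion that historical controls never had, and no common start date is stated for comparing the two groups

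*Protocol*

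**What the plan says.** The Study design section of the Protocol describes a "single institute prospective consecutive phase II clinical trial with matched historical controls", and Statistical methods repeats the design: "Prospective phase II clinical trial with matched historical controls". No section describes a randomization.

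Two places nevertheless rely on one. Under Secondary endpoint: "Overall survival is defined as the length of time from randomization to death from any cause". Under Withdrawal from treatment: "All patients that are randomised should be followed until the end points have been reached".

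The primary endpoint uses a different origin: "Progression free survival is defined as the length of time from inclusion to the first documentation of one of the following". The Flowchart places eligibility and consent in a single column, 3 months before radiotherapy. This matches the 3 months of neoadjuvant hormone treatment under Concomitant therapy.

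The comparison group is given in Study design: "A historical control group of 100 consecutive patients receiving external radiotherapy to prostate/pelvic lymph nodes", without the boost to the tumour. This group "will be used to compare PFS, OS, LC and QoL". Matching is on T stage, PSA before treatment and Gleason score. No index date is given for controls.

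**The concern.** A comparison of survival times needs time zero to mean the same thing in both groups. Here OS has a time zero that never occurs, and PFS has one that is an event of this prospective study. A historical patient has no inclusion date unless someone assigns one, and the Protocol does not say how.

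Two things are at stake. First, a difference in starting points passes directly into the estimated effect. If trial patients are timed from about 3 months before radiotherapy and controls from radiotherapy itself, the trial group is credited with a lead-in in which few events are expected. If controls are instead timed from an earlier date such as diagnosis, they carry the guaranteed survival, because each had to live long enough to receive radiotherapy. Second, the control date will have to be chosen at some point, possibly when control outcomes are already known. In a non-randomised comparison that is an avoidable degree of freedom.

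**Working it through.** **Start dates side by side**

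| Endpoint | Stated origin | Trial patients | Historical controls |
|---|---|---|---|
| OS | randomization | does not occur | does not occur |
| PFS | inclusion | about 3 months before radiotherapy (Flowchart) | no such event; no substitute stated |

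That controls lack an inclusion date is inferred from their being historical and from the Protocol's silence. It is not stated outright. The OS contradiction needs no inference.

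**The plan's own figure.** Power considerations gives 86 patients for a 20% improvement at three years, with 80% power and two-sided 0.05. The control rate is not given, nor whether 20% is absolute or relative, so 86 cannot be reproduced from stated inputs. Reading it as 20 points, the usual two-proportion formula gives 86 per group for an assumed 0.57 against 0.77 (also for 0.23 against 0.43). The present point does not depend on this number, and setting a common start date does not change it.

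**Illustration of a mismatch.** Inputs from the Protocol: a 3-month gap between inclusion and radiotherapy start, a 3-year time point, 86 trial patients and 100 controls. Assumptions: exponential PFS from radiotherapy start with the same hazard in both groups (no true effect), no events before radiotherapy, controls timed from radiotherapy start, and control 3-year PFS p of 50% to 70%.

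Thirty-six months on the trial clock is then 36 − 3 = 33 months of exposure to risk. With S(t) = exp(−λt) and λ = −ln(p)/36, the trial group shows S(33) = p^(33/36):

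| Control 3-year PFS | Apparent trial PFS | Spurious gain |
|---|---|---|
| 0.50 | 0.530 | 3.0 points |
| 0.60 | 0.626 | 2.6 points |
| 0.70 | 0.721 | 2.1 points |

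On the absolute reading of the 20% target, this is 2.1/20 to 3.0/20, or roughly 10% to 15% of the effect sought.

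**Effect on the error rate, control 0.60.** Standard error = √(0.60×0.40/100 + 0.626×0.374/86) = √(0.00240 + 0.00272) = 0.0716. The shift in standard errors is 0.0261/0.0716 = 0.364. Rejection favouring the trial group: P(Z > 1.96 − 0.364) = 5.5%, against a nominal 2.5%. Rejection in the other direction: P(Z < −1.96 − 0.364) = 1.0%. The total is about 6.5%, against 5%.

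**Sensitivity to the gap.** With 6 months the spurious gain is 4.3 to 6.1 points, and the chance of a false positive favouring the trial group is 9% to 13%. If controls were timed from a date close to trial inclusion, such as the start of hormone treatment, the mismatch would largely vanish. If they were timed from something earlier, it would change sign.

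**The case against.** The strongest reply is that the PFS origin is valid for the trial patients, that no section says controls will be timed from radiotherapy, and that assigning an index date to historical controls is often left to a statistical analysis plan, which is not at hand. Part of this stands: the size of any bias is conditional, and a mismatch is not a stated feature of the plan. It does not rescue the definitions. The Protocol commits to comparing PFS and OS between the groups, one of its two survival origins does not exist, and the other has no counterpart among the controls. That is wrong text in the endpoint section, not detail held back.

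A reader might infer three stronger points that the documents do not support:

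- *That OS follow-up stops at progression, so OS is censored just as the risk of death rises.* The Follow up section does let the six-monthly urology visits run until progression. But Withdrawal from treatment requires follow-up to the endpoints whatever later treatment is given, and the Flowchart's last column runs to the endpoint. Once the word for randomised is read as included, follow-up past progression is provided for. The two sections need aligning, no more.
- *That inclusion itself has two possible dates, because implanted markers are an inclusion criterion.* Functional imaging and the Flowchart both put inclusion before hormone treatment. The marker criterion conflicts with that order, but this is a conflict in the eligibility sequence and does not give PFS a second start.
- *That counting visits and the biopsy from the end of radiotherapy contradicts the endpoint origins.* It is ordinary scheduling.

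**Conclusion.** The point holds in this form: OS is timed from an event that happens to no one, PFS from an event that controls do not have, and the Protocol states no common start for either comparison. The OS error is a plain contradiction with the design. The PFS part rests on the absence of any control index date.

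The illustrated consequence is modest: 2.1 to 3.0 points on 3-year PFS and a two-sided error of about 6.5%. It depends on a control clock at radiotherapy start, exponential PFS of 50% to 70%, no events before radiotherapy and, for the comparison with the target, an absolute reading of 20%. None of these is stated in the Protocol, and the size and direction depend on the control date eventually chosen. It would be wrong to conclude that the primary comparison is known to be biased in favour of the boost. The definitions should be corrected before analysis because they are wrong as written and cheap to repair; the bias shown here is not large enough by itself to undermine the trial.

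**What to change.** Define PFS and OS in both groups from one clinical date recorded in both, and fix it before control outcomes are analysed. The first radiotherapy fraction is one candidate: every control has it by construction, and it should be in the treatment records. The start of hormone treatment would be another, if it is recorded for all controls. If radiotherapy start is used, state how included patients who never begin radiotherapy are handled, and report the trial group from inclusion, with all included patients, as a sensitivity analysis.

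In addition:

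- Replace the randomization wording under Overall Survival and Withdrawal from treatment with terms that fit the design.
- Align Follow up with Withdrawal from treatment, so that it is clear that vital status is followed after progression.
- Reconcile the marker criterion under Inclusion with the order of events in Functional imaging and the Flowchart.

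The cost is mainly redrafting, and the sample size is unchanged. With radiotherapy start as origin there are two real consequences. Trial-group times become about 3 months shorter than if counted from inclusion, and the main comparison becomes conditional on starting radiotherapy, which is why the analysis from inclusion should be reported beside it.

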#### *Safety*

At every follow up timepoint all adverse events will be documented and every effort will be made to collect patient charts if the patient has been treated outside our on centre.

#### *Quality of Life*

### Follow up

During the first year after treatment the patients will be seen by treating oncologist for clinical evaluation every 6 months ( $\pm$  14 days). Additional visits at treating physician’s discretion.

During the follow up between 12-60 months the patient may be referred to their home clinic and followed by urologist every 6 months ( $\pm$  28 days) or until progression. The 36 months-visit however, will take place at NUS, where a biopsy to investigate local control will be performed.

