#### *Local Control*

Local control is defined as negative biopsy 36 months after end of radiotherapy.

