**Flowchart**

| Investigation                                                     | 3 months
Pre RT | RT
start | Mid
RT | End of
RT | 6 months
after
end of
RT | 12 months
after end of
RT             | 18 months
after
end of
RT | 24 months
after
end of
RT | 30 months
after
end of
RT | 36 months
after
end of
RT | Every 6
month
until
endpoint |
|-------------------------------------------------------------------|--------------------|-------------|-----------|--------------|-----------------------------------|---------------------------------------------|------------------------------------|------------------------------------|------------------------------------|------------------------------------|---------------------------------------|
| Inclusion/Exclusion                                               | X                  |             |           |              |                                   |                                             |                                    |                                    |                                    |                                    |                                       |
| Informed consent                                                  | X                  |             |           |              |                                   |                                             |                                    |                                    |                                    |                                    |                                       |
| Androgen
deprivation therapy
GnRH                           | X                  | X           | X         | X            | End                               |                                             |                                    |                                    |                                    |                                    |                                       |
| Androgen
deprivation therapy,
antiandrogen                  |                    |             |           | Start        |                                   | End
Continuous
optional, dr
choice |                                    |                                    |                                    |                                    |                                       |

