| Instructions on
bowel, bladder
filling. Oral and
written |                    | X           |           |              |                                   |                                             |                                    |                                    |                                    |                                    |                                       |
| Prostate Biopsy,
optional                                      |                    | X           |           |              |                                   |                                             |                                    |                                    |                                    | X                                  |                                       |

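### The protocol gives conflicting stopping points for follow-up, putting overall survival, late toxicity and the 36-month biopsy at risk of incomplete, selective ascertainment after progression

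*Protocol*

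**What the plan says.** Three places in the protocol say when follow-up ends.

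- **Follow up.** After the first year the patient may be referred to the home clinic and seen by a urologist every six months, from month 12 to month 60, "or until progression. The 36 months-visit however, will take place at NUS, where a biopsy to investigate local control will be performed".
- **Withdrawal from treatment.** "All patients that are randomised should be followed until the end points have been reached - irrespective of further treatment regimes". The same section adds: "Loss of follow-up does not mean that the patient leaves the study".
- **Flowchart.** There are fixed columns up to 36 months after radiotherapy, then a last column headed "Every 6 month until endpoint". Which endpoint is meant is not said.

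Several outcomes can occur or fall due after a progression:

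- "Overall survival is defined as the length of time from randomization to death from any cause".
- "Local control is defined as negative biopsy 36 months after end of radiotherapy".
- Safety: adverse events are documented at each follow-up time point.
- Quality of life: forms are due up to five years.

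The Study design section compares PFS, OS, local control and quality of life with 100 historical controls. On the biopsy itself, the Follow up section says it will be done at 36 months, while the flowchart row reads "Prostate Biopsy, optional".

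**The concern.** Of the outcomes compared with the historical controls, only PFS is complete once a patient has progressed. A clinic that applies the visit rule literally stops at PSA progression, possibly years before death and before the 36-month biopsy is due. The patients no longer seen would be those with the higher risk of death and, probably, of local failure.

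Two consequences would follow:

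- **Survival.** Missing vital status after progression, handled as censoring, would be informative censoring, and survival would look too good.
- **Local control.** Patients who progressed before 36 months would drop out of the biopsy denominator, and the rate of negative biopsies would look too good.

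This is a question of data collection. An analysis plan cannot recover a biopsy that was not taken, and it can recover vital status only if someone arranges to obtain it.

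**Working it through.** **1. Side by side.** The Follow up section stops at progression. The Withdrawal section stops at the end points, whatever treatment follows. Since death is an endpoint, these differ for every patient who progresses and is still alive. The flowchart does not decide between them: its endpoint could be progression (the PFS event) or death.

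**2. Does the Withdrawal section override?** Not clearly. It is headed as a rule on withdrawal from treatment, and it refers to randomised patients in a trial without randomisation. The Follow up section is the operative visit schedule for the period when care may move to a home clinic. No flowchart row collects vital status.

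**3. Does the 36-month sentence rescue the biopsy?** Its word *however* can mark an exception to home-clinic referral only, or an exception to stopping at progression as well. Both readings fit. The flowchart's optional label then leaves the biopsy's completeness open even for patients who have not progressed.

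**4. Possible effect on overall survival.** The protocol states no figure to reproduce, and every rate here is an assumption:

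- freedom from progression at three years, S3: 60% to 77%
- death without progression, d0: 1% to 2% a year
- death after progression, d1: 8% to 15% a year

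The model has three states with constant hazards. The progression hazard is λ = −ln(S3)/3, which is 0.1703 for S3 = 0.60 and 0.0871 for S3 = 0.77.

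- True OS(t) = e^(−(λ+d0)t) + [λ/(λ+d0−d1)] × [e^(−d1·t) − e^(−(λ+d0)t)]
- Kaplan-Meier with every progressor censored at progression: e^(−d0·t)

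First row worked at t = 5: 0.406 + (0.1703/0.0303) × (0.472 − 0.406) = 0.406 + 0.373 = 0.779 (unrounded values used). Censored: e^(−0.05) = 0.951.

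| S3 | d0 | d1 | True 5-year OS | Censored at progression | Overstatement (points) |
|---|---|---|---|---|---|
| 0.60 | 0.01 | 0.15 | 0.779 | 0.951 | 17 |
| 0.60 | 0.02 | 0.15 | 0.750 | 0.905 | 15 |
| 0.77 | 0.02 | 0.08 | 0.858 | 0.905 | 5 |
| 0.77 | 0.01 | 0.08 | 0.895 | 0.951 | 6 |

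The other four combinations of these limits fall inside the same 5 to 17 points. If S3 is read as PFS including deaths, the range is about 4 to 16.

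**5. Possible effect on the biopsy.** With S3 of 77% to 60%, 86 × 0.23 = 20 to 86 × 0.40 = 34 patients would progress by three years. Those progressed and still alive at three years are 86 times the second term of the OS formula at t = 3: about 17 to 27 in the four rows above. These are the biopsies that would be missed if no progressed patient had one.

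For the bias, let S be three-year PFS, and fp and fn the local-failure rates in progressed and progression-free patients. The simple comparison, ignoring deaths, is:

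- Overstatement of local control = (1 − S) × (fp − fn)
- Smallest case assumed: S = 0.90, fp = 0.30, fn = 0.10, giving 0.10 × 0.20 = 2 points
- Largest case assumed: S = 0.60, fp = 0.50, fn = 0.10, giving 0.40 × 0.40 = 16 points

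**The case against.** The strongest reply is that stopping visits is not the same as censoring for survival. Overall survival runs to death from any cause, and nothing in the protocol prescribes censoring at progression or says that vital status stops being recorded. Even a patient lost to follow-up stays in the study, and *randomised* can hardly mean anyone but the enrolled patients. The progression clause may limit only the home-clinic arrangement. The flowchart's fixed columns to 36 months carry no progression stop, and the sentence on the 36-month visit may keep that visit for everyone. Quality-of-life forms have set dates with no progression condition, and the Safety section promises efforts to obtain charts from outside the centre.

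Much of this stands. A reader might infer that overall survival and the biopsy are definitely lost after progression. The documents do not support that: the loss follows only if the visit rule governs and nothing else supplies the data. A reader might also infer that the comparison with controls is tilted because control deaths come from records. The protocol does not say how control deaths are obtained, so only the trial group's own estimates can be discussed. Quality of life is the least exposed outcome, since its schedule is independent of progression.

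The conflict itself remains. Each reassuring reading is possible but none is stated, and the biopsy's optional label weakens the reading that it is kept for everyone. PFS as a time-to-event endpoint is not affected.

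**Conclusion.** The point holds as a conflict between passages with a conditional consequence. The Follow up section, the Withdrawal section and the flowchart give different or undefined stopping points, and the biopsy's status is inconsistent. If the visit rule is applied, overall survival, late toxicity and the 36-month biopsy are at risk of incomplete and selective recording. The likely direction is overstatement of the trial group's survival and local control, provided that death and local failure are more frequent after progression.

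The size cannot be fixed from the documents. The 5 to 17 points for five-year survival rest wholly on assumed hazards and on every progressor being censored. The 2 to 16 points for local control rest on assumed failure rates and on no progressed patient being biopsied. Both show scale under the worst handling and do not predict this trial's bias. The text should be corrected, because data not collected cannot be restored at analysis and the correction is cheap.

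**What to change.** 1. Reconcile the Follow up section, the Withdrawal section and the flowchart. State that vital status, late toxicity and quality of life are collected to 60 months irrespective of progression, by chart or registry where visits have stopped. Name the endpoint in the last flowchart column.
2. Add a survival-status field (alive or dead, date, source) to the CRF.
3. In the Withdrawal section, replace the reference to randomised patients with included patients, so that the rule plainly covers everyone in the trial.
4. Reconcile the Follow up section with the flowchart on whether the 36-month biopsy is planned for all or optional.
5. State how patients who progress before 36 months enter the local-control denominator.

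The cost is a few sentences in the protocol, one CRF field and a little extra data collection for patients who have progressed. Sample size and the definition of PFS do not change.
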